**APPENDIX B: SKIN-FOLD MEASUREMENT INSTRUCTIONS**

Instructions for use of Accu-Measure to measure skin-fold
[figure not shown]
thickness

- Before starting, ensure that the sliding marker on the Accu-Measure is set to zero millimeters.
- Grasp a section of skin in the upper deltoid closest to the area of vaccination
- Holding the skin between the thumb and forefinger of one hand, and gently squeeze the Accu-Measure over that skinfold with your other hand, until you hear an audible "click"
- The sliding marker on the Accu-Measure will indicate the exact thickness of your skinfold in millimeters
- If you are not confident about the accuracy of your measurement, reset the sliding marker to zero millimeters and repeat the procedure described above.
- Once a measurement has been obtained, use the table below to select the appropriate depth setting on the Tri-Grid Applicator
- Record skin-fold measurement in the medical record
- Wipe Acc-Measure device with an alcohol swab after each use

| Range of Measured **skin fold** Thickness [mm] | TriGrid Application Cartridge  Depth Selection |
| --- | --- |
| < 14 mm | A |
| 14-24 mm | B |
| 24-40 mm | C |
| >40 mm | Find alternate administration site or exclude from protocol |

**APPENDIX C: ADVERSE EVENT SEVERITY ASSESSMENT TABLE**

| **PARAMETER** | **MILD** | **MODERATE** | | **SEVERE** | |
| --- | --- | --- | --- | --- | --- |
| **General Principle for Severity Assessment** | Mild discomfort. Minimal or no limitation of daily activity.  No need for medical intervention. | Moderate discomfort.  Some limitation of daily activities (e.g. able to work part-time)  May require minimal or no medical intervention | | Severe discomfort. Marked limitation of daily activities (e.g. unable to work). Requires medical intervention. | |
| **LOCAL REACTOGENICITY:** | | |  | |  |
| **Pain and tenderness** | Minimal discomfort associated with minimal or no limitation of use of arm | Moderate discomfort with some limitation of use of arm causing some interference with daily activities. May require single dose of analgesic or NSAID. | | Severe discomfort with significant limitation of use of arm causing marked limitation of daily activities (e.g. unable to work). Requires medical intervention (e.g. repeated doses of analgesic or NSAID). | |
| **Erythema (redness) or skin discoloration** | Light red blush up to 25% of the circumference of the upper arm | Marked redness involving up to 50% of the circumference of the arm | | Brick red involving >50% of the circumference of the upper arm | |
| **Edema (swelling)** | Light edema involving up to 25% of the circumference of the upper arm | Marked edema involving up to 50% of the circumference of the arm | | Significant edema >50% of the circumference of the upper arm | |
| **Induration** | Hardening under the skin <1.5 cm in diameter | Hardening under the skin 1.5-3.0 cm in diameter | | Hardening under the skin >3.0 cm in diameter | |
| **Skin damage (vesicle, ulcer)** | Vesicles or superficial disruption of epithelium < 1 cm | Vesicles or superficial disruption of epithelium 1-2 cm | | Full thickness disruption of the epithelium (ulceration) > 2 cm | |
| **Formation of crust, scab or scar** | Crust, scab or scar = 2cm | Crust, scab or scar 2­4cm | | Crust, scab or scar > 4cm | |

| **SYSTEMIC REACTOGENICITY** | |  |  |
| --- | --- | --- | --- |
| **Headache** | Minimal headache causing no interference with daily activities | Moderate headache causing some interference with daily activities. May require single dose of analgesic or NSAID. | Significant headache causing marked limitation of daily activities (e.g. unable to work). Requires medical intervention (e.g. repeated doses of analgesic or NSAID). |
| **Rigor (chills)** | Minimal discomfort causing no interference with daily activities | Moderate discomfort causing some interference with daily activities | Significant discomfort causing limitation with daily activities (e.g. unable to work). |
| **Malaise (generalized feeling of discomfort)** | Minimal discomfort causing no interference with daily activities | Moderate discomfort causing some interference with daily activities | Significant discomfort causing limitation with daily activities (e.g. unable to work). |
| **Fatigue (tiredness)** | Minimal discomfort causing no interference with daily activities | Moderate discomfort causing some interference with daily activities | Significant discomfort causing limitation with daily activities (e.g. unable to work). |
| **Myalgia (other than vaccination site)** | Minimal muscle pain causing no interference with daily activities | Moderate muscle pain causing some interference with daily activities. May require single dose of analgesic or NSAID. | Significant muscle pain causing marked limitation of daily activities (e.g. unable to work). Requires medical intervention (e.g. repeated doses of analgesic or NSAID). |
| **Arthralgia** | Minimal joint pain causing no interference with daily activities | Moderate joint pain causing some interference with daily activities. May require single dose of analgesic or NSAID. | Significant joint pain causing marked limitation of daily activities (e.g. unable to work). Requires medical intervention (e.g. repeated doses of analgesic or NSAID). |
| **Fever** | 37.7–38.6°C (99.8– 101.5°F) | 38.7–39.3°C (101.6– 102.7°F) | >39.4°C (>102.8°F) |
| **Nausea** | Minimal nausea causing no interference with daily activities | Moderate nausea causing some interference with daily activities.. | Significant nausea causing marked limitation of daily activities (e.g. unable to work). |

| **Vomiting** | Minimal nausea causing no interference with daily activities | Moderate nausea causing some interference with daily activities. | Significant nausea causing marked limitation of daily activities (e.g. unable to work). Requires medical intervention |
| --- | --- | --- | --- |
| **Pruritus** | Localized itching at vaccination site | Itching at the injected arm (beyond vaccination site) | Generalized itching |
| **Rash** | Localized maculopapular (non­urticarial) rash at the vaccination site area causing no interference with daily activities | Diffuse maculopapular (non-urticarial) rash at the injected arm (beyond vaccination site) causing some limitation of daily activities | Systemic maculopapular (non­urticarial) rash causing marked limitation of daily activities. Requires medical intervention |
| **Allergic reaction** | Localized urticaria at vaccination site causing no interference with daily activities | Diffuse urticaria at the injected arm (beyond vaccination site) and causing some limitation of daily activities | Systemic urticaria or angioedema causing marked limitation of daily activities. Requires medical intervention |
| **HEMATOLOGY** |  |  |  |
| Hemoglobin | 10.0 g/dL – 11.0 g/dL OR  any decrease = 2.5 g/dL | 9.0 g/dL – 9.9 g/dL OR  any decrease = 3.5 g/dL | = or <8.9 g/dL  OR  any decrease = 4.5 g/dL |
| WBC—Elevated WBC—Decreased | 13,000–14,999/mm3 | 15,000–19,999/mm3 | = or >20,000/mm3 |
| 2000–2499/mm3 | 1500–1999/mm3 | = or <1499/mm3 |
| Absolute Neutrophil Count | 1000–1300/mm3 | 750–999/mm3 | = or <749/mm3 |
| Absolute Lymphocyte Count | 600–649/mm3 | 500–599/mm3 | = or <499/mm3 |
| Absolute CD4 Count (HIV Negative) | 300–400/mm3 | 200–299/mm3 | = or <199/mm3 |
| Platelets—Decreased Platelets—Elevated | 100,000–124,999/mm3 | 50,000–99,999/mm3 | = or <49,999/mm3 |
| NA | 550,000–600,000/mm3 | > 600,000/mm3 |
| **CHEMISTRY** |  |  |  |
| BILIRUBIN (total) | 1.0–1.5 x ULN | >1.5–2.5 x ULN | >2.5 x ULN |
| CREATININE | 1.1–1.3 x ULN | >1.3–1.8 x ULN | >1.8 x ULN |
| AST (SGOT) | 1.51–3.0 x ULN | >3.0–6.0 x ULN | >6.0 x ULN |
| ALT (SGPT) | 1.51–3.0 x ULN | >3.0–6.0 x ULN | >6.0 x ULN |
|  |  |  |  |

| **URINALYSIS** | | |  | |  |
| --- | --- | --- | --- | --- | --- |
| PROTEINURIA | 1+ (30 mg/dL) | 2–3+ (100-500mg/dL) | | 4+ (> 500mg/dL) | |
| Random urine 24-hour urine | 200 mg–500 mg loss/day | > 500 mg–1.0 g loss/day | | > 1.0g loss/day | |
| HEMATURIA (in the absence of vaginal bleeding) By microscopic exam only | 1+ (ca. 5–10 Ery/mL) 6-10 Ery/hpf | 2+ (ca. 10–25 Ery/µl) >10 Ery/hpf | | 3+ (ca. 50 Ery/µl) Gross, with or without clots or RBC casts | |
| GLUCOSURIA | 1+ (30mg/dl, 2.8 mmol/L) | 2+ (100mg/dL, 5.5mmol/L) | | 3+ (300mg/dL, 17 mmol/L) | |
| LEUCOCYTURIA | 1+ (ca. 10–25 Leuco/mL) | 2+ (ca. 75 Leuco/mL) | | 3+ (ca. 500/mL) | |
| **CARDIOVASCULAR** | | | | | |
| Hypotension | Transient orthostatic hypotension with heart rate increased > 20 beats/min **OR** Decreased by >10mm Hg systolic BP, No Rx required | Symptoms **OR** BP decreased by >20 mm Hg systolic, correctable with oral fluid Rx | | IV fluid required **OR** Hospitalization | |
| Hypertension | Asymptomatic, transient increase by >20 mmHg diastolic BP **OR** >150/100 if previously normal. No treatment required. | Recurrent or persistent or symptomatic increase by >20 mmHg diastolic BP **OR** >150/100 if previously normal. Treatment required. | | More intensive treatment required **OR** more than one drug required **OR** requires acute treatment | |
| Cardiac Arrhythmia | Asymptomatic with transient dysrhythmia causing no interference with daily activities. No treatment required. | Notable symptoms causing some interference with daily activities. Non-urgent treatment required | | Symptomatic and incompletely controlled by medical or invasive treatment. | |
| Pericarditis | Minimal asymptomatic effusion | More than minimal asymptomatic effusion requiring no treatment | | Symptomatic effusion, pain, EKG changes. | |
| Hemorrhage, blood loss | Asymptomatic and requiring no therapy | Mildly symptomatic | | Gross blood loss **AND/OR** 1–2 units transfused | |

| **GASTROINTESTINAL** | |  |  |
| --- | --- | --- | --- |
| Constipation | Minimally symptomatic. No medical intervention required. | Significant abdominal pain with impaction requiring prescription | Requiring disimpaction **AND/OR** Hospital treatment |
| Diarrhea | Mild or transient or intermittent episodes (2-3/day)of unformed stools resulting in minimal or no interference with daily activities | Persistent episodes (5­10/day)of unformed-to-watery stools resulting in greater than minimal interference with daily activities | Bloody diarrhea or >10/day episodes. **AND/OR** Orthostatic hypotension **AND/OR** Electrolyte imbalance requiring IV fluid/therapy |
| Oral Discomfort/Dysphagia | Mild discomfort, no difficulty swallowing | Difficulty swallowing but able to eat and drink | Unable to swallow solids |
| **NEUROLOGICAL** | | | |
| Neuropsychiatric/mood | Mild mood alteration not interfering with daily activities. No intervention required. | Depression or anxiety symptoms causing individual to seek attention and be treated with counseling and/or pharmacotherapy | Severe mood changes requiring additional medical intervention **AND/OR** Suicidal ideation/gesture |
| Paresthesia (burning, tingling, etc.) | Minimal discomfort resulting in minimal or no interference with daily activities | Notable symptoms resulting in greater than minimal changes in daily activities | Marked and persistent discomfort resulting in significant incapacity **AND/OR** Narcotic analgesia required for symptomatic improvement |
| Neuro-motor | Mild weakness resulting in minimal or no interference with daily activities | Moderate weakness resulting in greater than minimal interference with daily activities | Significant incapacity |

| Neuro-sensory | Mild impairment (decreased sensation) resulting in minimal or no interference with daily activities | | Moderate impairment resulting in greater than minimal interference with daily activities | | Significant incapacity |
| --- | --- | --- | --- | --- | --- |
| Neuro-cerebellar | Slight incoordination **OR** Dysdiadochokinesia | | Intention tremor **OR** Slurred speech **OR** Nystagmus | | Ataxia requiring assistance to walk or arm incoordination interfering with daily life activities |
| **RESPIRATORY** | | | | | |
| Cough | Transient cough resulting in minimal or no interference with daily activities | | Recurrent or persistent cough resulting in greater than minimal interference with daily activities | | Uncontrolled cough causing significant interference with daily activities |
| Bronchospasm Acute | Transient not requiring treatment. FEV1 or peak flow reduced to 70–80% | | Treatment required ­normalizes with bronchodilator. FEV1 or peak flow 50– 69% | | More intensive treatment required ­no normalization with bronchodilator. FEV1 or peak flow < 50% |
| Dyspnea | Dyspnea on exertion (such as using stairs) | | Dyspnea with normal activity (such as walking) | | Dyspnea at rest |
| **MISCELLANEOUS** | | | | | |
| Arthritis | Mild pain with no joint swelling. No interference with daily activities. | | Moderate pain with inflammation, erythema, or joint swelling. Some interference with daily activities. | | Severe pain with inflammation, erythema, or joint swelling causing significant incapacity. |
| Eye | Symptoms resulting in minimal or no interference with daily life activities | | Notable symptoms resulting in greater than minimal interference with daily life activities | | Symptoms (such as loss of vision, clinically diagnosed uveitis, or glaucoma) resulting in significant incapacity |
| Skin (general) | Localized, asymptomatic. | | Diffuse with notable symptoms and/or some interference with daily activities. | | Generalized, marked symptoms and/or significantly interference with daily activities. |
| **ADDITIONAL LABORATORY ABNORMALITIES** | | | | | |
| Fibrinogen—Elevated | 450–600 mg/dL | 601–650 mg/dL | | > 650 mg/dL | |
| Fibrinogen—Decreased | 100–200 mg/dL | < 100 mg/dL | | < 75 mg/dL | |

| Prothrombin Time (PT) | 1.1–1.24 x ULN | 1.25–1.49 x ULN | = or >1.5 x ULN |
| --- | --- | --- | --- |
| PTT | 1.1–1.66 x ULN | 1.67–2.33 x ULN | = or >2.34x ULN |
| BUN | 25–30 mg/dL | 31–40 mg/dL | = or >41 mg/dL |
| LDH | 1.5–2.5 x ULN | 2.6–3.5 x ULN | = or >3.6 x ULN |
| Hyponatremia | 130–135 meq/L | 123–129 meq/L | = or <124 meq/L |
| Hypernatremia | 146–150 meq/L | 151–157 meq/L | = or >158 meq/L |
| Hyperkalemia | 5.0–5.5 meq/L | 5.6–6.0 meq/L | = or >6.1 meq/L |
| Hypokalemia | 3.2–3.4 meq/L | 3.0–3.1 meq/L | = or <2.9 meq/L |
| PHOSPHATE Hypophosphatemia | 2.0–2.4 mg/dL | 1.5 –1.9 mg/dL | = or <1.4 mg/dL |
| Hypocalcemia | 7.8–8.4 mg/dL | 7.0–7.7 mg/dL | = or <6.9 mg/dL |
| Hypercalcemia | 10.6–11.5 mg/dL | 11.6–12.5 mg/dL | = or >12.6 mg/dL |
| Hypomagnesaemia | 1.2 –1.4 meq/L | 0.9–1.1 meq/L | = or <0.8 meq/L |
| Hypoglycaemia | 3.1–3.6 mmol/L (55–64 mg/dL) | 2.2–3.0 mmol/L (40–54 mg/dL) | = or <2.1 mmol/lL(= or <39 mg/dL) |
| Hyperglycaemia (nonfasting and no prior diabetes | 6.5–9.0 mmol/L (116–160 mg/dL) | 9.1–14.0 mmol/L (161–250 mg/dL) | = or >14.1 mmol/l (= or >251 mg/dL) |
| Triglycerides | NA | 400–750 mg/dL | = or >751 mg/dL |
| Hyperuricemia | 7.5–10.0 mg/dL | 10.1–12.0 mg/dL | = or >12.1 mg/dL |
| GGT | 1.25–2.5 x ULN | 2.6–5.0 x ULN | = or >5.1 x ULN |
| Alkaline Phosphatase | 1.25–2.5 x ULN | 2.6–5.0 x ULN | = or >5.1 x ULN |
| Amylase | 1.1–1.5 x ULN | 1.6–2.0 x ULN | = or >2.1 x ULN |
| Pancreatic amylase | 1.1–1.5 x ULN | 1.6–2.0 x ULN | = or >2.1 x ULN |
| Lipase | 1.1–1.5 x ULN | 1.6–2.0 x ULN | = or >2.1 x ULN |

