**d) Primary Endpoints**

**Safety and Tolerability**:

- Severe local reactogenicity events (pain, tenderness, erythema/skin discoloration, edema, damage [vesiculation/ulceration], induration, formation of a crust or scab.
- Severe systemic reactogenicity events (fever, chills, headache, nausea, vomiting, malaise, myalgia, arthralgia, rash).
- Severe other adverse events (including laboratory abnormalities).
- All Serious Adverse Events.
- Proportion of volunteers with mild and moderate local and systemic reactogenicity events.
- Electroporation Tolerability Assessment Questionnaire Responses (Appendix B)

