**Exclusion Criteria:**

1. Confirmed HIV-1 or HIV-2 infection
2. Any clinically significant abnormality on history or examination including history of immunodeficiency or autoimmune disease; use of systemic corticosteroids immunosuppressive, anticancer, or other medications considered significant by the trial physician within the last 6 months
3. Any clinically significant acute or chronic medical condition requiring care of a physician (e.g., diabetes, coronary artery disease, rheumatologic illness, malignancy, substance abuse) that in the opinion of the investigator would preclude participation
4. Any laboratory value outside of reference range, with the exception of any non-clinically significant Grade I elevations of liver function tests (AST, ALT, direct/total bilirubin), CBC, and urinalysis, as determined by the Principal Investigator or his designee
5. Confirmed diagnosis of hepatitis B (surface antigen, HbsAg); hepatitis C (HCV antibodies) or active syphilis
6. If female, pregnant, planning a pregnancy during the trial period, or lactating
7. Receipt of a live attenuated vaccine (other than influenza) within 30 days or other vaccine within 14 days of ADVAX vaccination
8. Receipt of blood transfusion or blood products 6 months prior to vaccination
9. Participation in another clinical study of an investigational product currently or within past 12 weeks, or expected participation during this study
10. History of severe local or systemic reactogenicity to vaccination or history of severe allergic reactions
11. Major psychiatric illness including any history of schizophrenia or severe psychosis, bipolar disorder requiring therapy, suicidal attempt or ideation in the previous 3 years
12. Any electronic stimulation device, such as cardiac demand pacemakers, automatic implantable cardiac defibrillator, nerve stimulators, or deep brain stimulators
13. Individuals in which a skin-fold measurement of the cutaneous and subcutaneous tissue for all eligible injection sites (deltoid muscles with intact lymph drainage) exceeds 40 mm
14. In the opinion of the investigator, unlikely to comply with protocol

12. **Recruitment and Consent Procedures**:

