No more than one volunteer per day will be enrolled for the first four volunteers to receive electroporation in each dose group. For these four volunteers, an additional telephone call to assess safety and adverse events will be made on the day following vaccination. If four vaccinations by electroporation have occurred without greater than moderate adverse events, the remainder of the group can be enrolled with no fixed interval between volunteers.

A. **Description of Adverse Events (AE) Detection and Reporting:**

**i. Adverse Event Definition**: An adverse event is any noxious, pathologic, or unintended change in anatomical, physiologic, or metabolic functions, as indicated by physical signs, symptoms, and/or laboratory changes occurring in any phase of the clinical trial, whether associated with drug and whether or not considered drug related. All of the following are to be considered adverse events:

- An exacerbation of a pre-existing condition.
- An inter-current illness.
- Any drug interaction.
- Any event related to a concomitant medication.
- Development of an abnormal laboratory value or a significant change from baseline in a laboratory value within the range of normal, considered by the investigator to be clinically important.

Any adverse event prior to the first vaccination will be reported as a pre-existing condition on the “previous conditions” source document. At each outpatient visit, subjects will be questioned and/or examined by the PI or his designee for evidence of AEs. The onset and end dates, severity and relationship to study vaccine and EP device will be recorded in the medical record for each event.

**ii. Assessment of Severity:** The severity of the AE will be assessed according to the Adverse Event Severity Assessment Table (see Appendix C).

**iii. Serious Adverse Event (SAE) Definition:** An SAE is an AE that results in any of the following outcomes.

- Death
- Life threatening condition
- Hospitalization or prolongation of stay
- Persistent or significant disability or incapacity
- Congenital anomaly or birth defect
- Medically significant event, including laboratory abnormalities

Important medical events that do not result in death, are life threatening, or require hospitalization, may be considered SAEs when, based on appropriate medical judgment, they may jeopardize the volunteer, or may require medical/surgical intervention to prevent one of the outcomes listed in this definition.

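### Appendix C grades vomiting with nausea wording and pairs two different temperatures at the severe-fever limit, both in components of the primary reactogenicity endpoint; exclusion 4 also conflicts with the AST/ALT bands

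*Protocol*

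**What the plan says.** Section d) Primary Endpoints counts "Severe systemic reactogenicity events (fever, chills, headache, nausea, vomiting, malaise, myalgia, arthralgia, rash" and also "Proportion of volunteers with mild and moderate local and systemic reactogenicity events". All three grades are therefore endpoint data, and vomiting and nausea are separate items. The Data and Safety Monitoring Plan (section 14, item A.ii) names the instrument: "The severity of the AE will be assessed according to the Adverse Event Severity Assessment Table", which is Appendix C.

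In Appendix C the Vomiting row gives, for mild, "Minimal nausea causing no interference with daily activities" and, for moderate, "Moderate nausea causing some interference with daily activities". Its severe cell describes significant nausea that markedly limits activity, and adds a need for medical intervention.

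In the Fever row, mild is 37.7–38.6 °C (99.8–101.5 °F), moderate is 38.7–39.3 °C (101.6–102.7 °F), and severe is ">39.4°C (>102.8°F".

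Exclusion 4 bars any laboratory value outside the reference range, "with the exception of any non-clinically significant Grade I elevations of liver function tests", CBC and urinalysis, as the investigator determines. Appendix C starts the mild band for AST and ALT at 1.51 × ULN.

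**The concern.** A severity table is the measuring rule for a reactogenicity endpoint. If a row describes a different symptom, the recorded grade does not measure the item it is filed under. If a boundary is given as two unequal temperatures, the grade can depend on which scale the grader reads.

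The same grades are used beyond the final tabulations:
- **Enrolment pacing.** Enrolment of the rest of each dose group depends on the first four electroporation volunteers having no event above moderate (section 14; repeated in section 15).
- **DSMB listing.** Before each teleconference the DSMB receives events of grade 2 or higher.
- **Suspension.** The trial is suspended once three volunteers have an SAE or severe event judged both related and clinically significant.

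The exclusion 4 issue concerns eligibility rather than the endpoint, but it comes from the same table.

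**Working it through.** **Vomiting row against Nausea row**

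| Grade | Nausea row | Vomiting row |
|---|---|---|
| Mild | "Minimal nausea causing no interference with daily activities" | identical |
| Moderate | "Moderate nausea causing some interference with daily activities" | identical |
| Severe | significant nausea, marked limitation | same, plus need for medical intervention |

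No Vomiting cell refers to vomiting. Each does carry a second element, the effect on daily functioning, and the severe cell adds intervention. Two cases follow. A volunteer who vomits with little nausea but loses some activity meets the functional half of the moderate cell and fails its symptom half. A volunteer with nausea alone meets the wording of both rows.

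**Fever limits.** Inputs are the five printed pairs. Formula: F = C × 9/5 + 32.

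| Printed °C | Computed °F | Printed °F | Reproduced? |
|---|---|---|---|
| 37.7 | 99.86 | 99.8 | yes, by truncation |
| 38.6 | 101.48 | 101.5 | yes, by rounding |
| 38.7 | 101.66 | 101.6 | yes, by truncation |
| 39.3 | 102.74 | 102.7 | yes, either way |
| 39.4 | 102.92 | 102.8 | no; 102.9 either way |

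In reverse, (102.8 − 32) × 5/9 = 39.33 °C. Only the severe limit fails to reproduce.

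Next, each 0.1-degree reading near the boundary is graded on each scale as printed, with Celsius rounded to one decimal:

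| Reading | Grade in °F | Equivalent °C | Grade in °C |
|---|---|---|---|
| 102.8 °F | none | 39.33, so 39.3 | moderate |
| 102.9 °F | severe | 39.39, so 39.4 | none |
| 103.0 °F | severe | 39.44, so 39.4 | none |

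From the lower mild limit upward, the only ungraded readings are 102.8 on the Fahrenheit scale and 39.4 on the Celsius scale. The diary card records temperature in °F, so 102.8 °F is a value it can contain.

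If the severe cell was meant to include its own limit, both gaps close. 102.8 °F then becomes severe in °F but stays moderate in °C, because 39.3 °C is in the moderate band. The mismatch remains.

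**Exclusion 4.** Take ULN as the upper end of the reference range and Grade I as the mild column of Appendix C. An ALT of 1.2 × ULN is out of range and below 1.51 × ULN, so it is not Grade I; the exception does not apply and the volunteer is excluded. An ALT of 1.51–3.0 × ULN is Grade I and may be admitted if not clinically significant. The lower value is barred while the higher may pass. Total bilirubin shows no such inversion, because its mild band starts at 1.0 × ULN.

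**Scale of one changed grade.** 1/8 = 12.5 percentage points in a group of 8.

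**The case against.** The best reply is that the table still works in practice.

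**Vomiting.** Every cell carries a functional criterion consistent with the General Principle row at the head of the table. The diary card lists nausea and vomiting on separate lines, with a general functional code that does not mention nausea. This stands in part: vomiting that stops a volunteer working does not meet a mild cell that requires no interference. A reader might infer that vomiting cannot be graded, or that nausea and vomiting collapse into one measure. The documents support neither: the fallback exists, the diary lines are separate, and the severe cells differ. The fallback still leaves each grader to choose between a specific row on the wrong symptom and a general row, and two graders may differ.

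**Fever.** The gap is one reading per scale, and a grader who converts can resolve it: 102.8 °F becomes 39.3 °C (moderate), and 39.4 °C becomes 102.92 °F (severe). A lost sign is also possible. The rat study report says samples were pooled with fewer than 5 like samples, yet puts 16 muscle samples into three pools. Fewer than 5 others means at most 5 per pool, so 3 × 5 = 15; at most 5 others allows 3 × 6 = 18. That suggests an inequality lost its equality part elsewhere in this text. Against this, the table writes such limits as an equals sign followed by the inequality in many rows, and a greater-or-equal sign survives in the risks section. The point is open, so the gap is claimed only conditionally. The unequal temperatures do not depend on it, and conversion and a restored sign give 102.8 °F different grades.

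**Consequences.** A reader might infer that the rule removing volunteers for reactions of Grade 3 or above is affected. That rule, in the risks section, concerns injection reactions in a paragraph on local site effects, so vomiting and fever are not shown to reach it. The 12.5-point figure applies to any misgrade and says nothing about likelihood, and the analysis is mainly descriptive.

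**Exclusion 4.** The criterion leaves the exception to the investigator. That discretion decides which Grade I values are acceptable; on its literal wording it does not extend the exception to values below Grade I.

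**Conclusion.** The point holds in limited form. The Vomiting row is wrong as written, and it governs a named component of the primary endpoint. The row applies to every vomiting event, but the number that would receive a different grade cannot be derived from the protocol. The severe-fever limit is internally inconsistent by 0.12 °F (102.92 − 102.8). Its ungraded readings are 102.8 °F and 39.4 °C, conditional on the printed sign being the sponsor's own. These faults can reach the severity tabulations, the first-four enrolment step and the DSMB listing. They reach the suspension count only for severe events also judged related and clinically significant. The DSMB link assumes that grade 2 means moderate.

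Exclusion 4 and the AST/ALT bands contradict each other for values above 1.0 and below 1.51 × ULN, assuming that Grade I means the mild column.

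Other irregularities in the table do not add weight. Diarrhea jumps from 2–3 to 5–10 episodes a day, but it is not a listed reactogenicity item and its cells carry functional criteria. The fibrinogen overlap is nested, so the worse grade is the natural reading.

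**What to change.** The sponsor should:
- replace the three Vomiting cells with criteria that refer to vomiting;
- make the fever bands contiguous, with the same limits in °C and °F, so that each reading has one grade whichever scale is used;
- reconcile exclusion 4 with the AST/ALT bands and state that Grade I means the mild column, if it does.

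The cut-offs and clinical criteria are for the sponsor to choose; none is proposed here.

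The cost is a correction to one appendix table and one eligibility cross-reference, with no new visits, assays or data. The rationale section reports that vaccinations have already been tolerated in all dose groups, so some events may already have been graded. If so, recorded vomiting events and any temperatures from 102.8 to 103.0 °F (or at 39.4 °C) should be rechecked against the corrected rows.

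### Appendix C grades rash confined to the injection site or injected arm as mild or moderate systemic reactogenicity, so a local finding enters the systemic half of a primary endpoint

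*Protocol*

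**What the plan says.** Section 14 of the protocol (Assessment of Severity) makes Appendix C the table by which adverse events are graded. In that table the block headed "SYSTEMIC REACTOGENICITY" runs until the hematology rows and contains Pruritus, Rash and Allergic reaction.

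- **Rash.** The mild cell ends "rash at the vaccination site area causing no interference with daily activities", the moderate cell "rash at the injected arm (beyond vaccination site) causing some limitation of daily activities", and the severe cell, which requires systemic spread, "rash causing marked limitation of daily activities. Requires medical intervention".
- **Pruritus.** Mild is "Localized itching at vaccination site", moderate extends to the injected arm, and severe is "Generalized itching" with no further condition.
- **Allergic reaction.** The same pattern applies to urticaria: site, injected arm, then systemic with marked limitation and intervention.

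Section d) Primary Endpoints includes "Severe systemic reactogenicity events (fever, chills, headache, nausea, vomiting, malaise, myalgia, arthralgia, rash" and, as a separate item with no symptom list of its own, "Proportion of volunteers with mild and moderate local and systemic reactogenicity events". Its local list covers pain, tenderness, erythema or discoloration, edema, skin damage, induration and crusting. It has no entry for rash, itching or urticaria, and neither does the local block of Appendix C.

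**The concern.** The primary endpoint separates local from systemic tolerability. For rash, the systemic block defines its two lower grades by anatomical confinement to the place where the needle and electrodes go in. Every mild or moderate rash that fits that row is therefore local in extent but carries a systemic label.

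The same block handles another symptom differently: its Myalgia row expressly leaves out muscle pain at the vaccination site. The skin rows depart from that principle without explanation.

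What is at stake is the meaning of one column in a safety table. Section g) (Analysis) describes the analysis as mainly descriptive, so the counts are the result and no later step corrects a wrong label.

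**Working it through.** The protocol gives no figure on this point to reproduce. The check is a comparison of sections, followed by arithmetic for scale.

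**Tracing cases through the text**

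1. *Maculopapular rash at the injection site, no effect on activity.* It meets the mild cell of the Rash row. The row is in the systemic block, and section d) names rash as systemic and not as local. Result: a mild systemic event.
2. *Maculopapular rash spreading over the injected arm, some limitation.* It meets the moderate cell. Result: a moderate systemic event.
3. *Generalized rash without marked limitation.* Mild requires the site, moderate requires the injected arm, and severe requires systemic spread together with marked limitation and intervention. It fits no cell of the Rash row. Generalized urticaria without marked limitation has the same gap in the Allergic reaction row.
4. *Slight generalized itching.* It meets the severe cell of the Pruritus row, which sets no condition on intensity or limitation.
5. *Can a site-confined finding reach the severe systemic count?* No. The severe cells of all three rows require generalized or systemic extent.

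**Scale**

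Input: 8 volunteers per group (section f) Study Design).

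- One misclassified volunteer with no other systemic event moves the proportion by 1/8 = 12.5 percentage points.
- Exact (Clopper-Pearson) 95% intervals are 0 to 0.37 for 0/8, 0.003 to 0.53 for 1/8, and 0.03 to 0.65 for 2/8. The point estimate moves visibly, but the intervals overlap heavily.
- The protocol gives no rate of site-confined maculopapular rash. If that rate were r per volunteer, the chance of at least one in a group of 8 would be 1 − (1 − r)^8. For r = 5%, 10% and 20% (assumptions only) this is 1 − 0.95^8 = 34%, 1 − 0.90^8 = 57% and 1 − 0.80^8 = 83%.

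**The case against.** The other side has several good points.

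- **Scope.** Section d) names only rash. Section 14 uses Appendix C for severity and does not say that its block headings assign endpoint class. Itching and urticaria therefore enter only if the mild and moderate endpoint is read as covering the whole block. This stands. For rash the objection fails, because section d) itself places rash on the systemic side.
- **Ordinary redness is not affected.** The Rash row is limited to maculopapular, non-urticarial rash. Redness and discoloration have their own local row and local endpoint term. This stands and narrows the set of affected events. Rash is also absent from the volunteer diary card, so nothing in the protocol points to a high rate.
- **A grade can be found elsewhere.** A reader might infer from cases 3 and 4 that true mild systemic rash cannot be graded or is lost. The documents do not support that. The General Principle row of Appendix C carries no site condition and can supply a grade. The Skin (general) row covers diffuse findings with notable symptoms, though its own mild cell is also localized. Section g) (Safety and Tolerability) has all adverse events reported. What remains is that the specific rows and the general rows do not agree.
- **Bias between arms.** A reader might infer that electroporation will appear to cause systemic reactions that conventional injection does not. The risk section does expect that electroporation may increase local site reactions, but it predicts no maculopapular rash. All arms are graded by the same table, IM recipients also have an injection site, and the saline/EP group shares the device. The protocol itself concedes very limited power to compare event rates between arms. A differential effect is possible but not shown.

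**Conclusion.** The inconsistency is real and minor. Read as written, section d) and Appendix C together count a maculopapular rash confined to the injection site or injected arm as mild or moderate systemic reactogenicity in a primary endpoint. In a group of 8, each volunteer with no other systemic event who is counted this way adds 12.5 percentage points.

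For rash, this rests only on the text. For itching and urticaria, it rests on reading the mild and moderate endpoint as covering the whole systemic block. The severe systemic endpoint is not inflated by site findings, and sample size and power are untouched. How often site rash occurs, and whether it differs between EP and IM, is unknown, so no overall inflation factor can be stated.

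**What to change.** 1. **Classification.** In section d) and Appendix C, classify and tabulate rash confined to the vaccination site or injected arm as local reactogenicity, together with itching and urticaria if they are counted. Count only findings beyond the injected arm as systemic, in line with how the Myalgia row treats the vaccination site. Extent is already part of the grading text, so no new data are needed. The relabelled events keep their mild or moderate grade.
2. **Reconciliation of grades.** Once the confined findings are local, the three rows hold no mild or moderate cell for a systemic finding. The sponsor should therefore also reconcile the Rash, Pruritus and Allergic reaction rows with the General Principle and Skin (general) rows. No severity rule is proposed here, because grades feed the staggered enrolment in the Safety Review Plan (section 14) and the suspension trigger under the indications for discontinuing vaccinations.

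The cost is a small wording change to three rows and to the endpoint lists. Tabulations would differ slightly from those of any earlier trial that used the same table.
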